## **9.2 Collection, Recording and Reporting**

### **9.2.1 AE**

AEs will be collected from the time the informed consent and assent forms have been signed until the end of the study. This will include AEs spontaneously reported by the subject and / or observed by the parents and clinicians.

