### 3.3 Withdrawal Criteria

Subjects may be withdrawn from the intervention according to the discretion of the Principal Investigator if:

1. ADHD-RS raw score increases by 25% as rated by clinicians, and/or
2. CGI-S scores are between 5 and 7 inclusive.
3. Receive any medication (e.g. methylphenidate, atomoxetine, tricyclic anti-depressant, and/or polyunsaturated fatty acids (PUFA) supplement (e.g. Omega-3 oil, flax seed oil, cod liver oil), and/or traditional Chinese medication (TCM) which can improve ADHD symptoms during the trial period. The parent/child will be asked about this each time they turn up at the clinic.

All recruited subjects are free to withdraw consent and discontinue participation without penalty and without providing reasons. However data collection will continue after withdrawal from intervention unless the subject or parents/legal guardians decide to withdraw from the study totally (this will be explicitly asked again upon withdrawal).

Participants can still choose to continue or discontinue with the remaining assessments at Week 1, 8, 16 (control), 20 (intervention), 24 (intervention), 28 (control), and 32 (control) despite having BCI training sessions being ceased.

Subjects will be considered as 'drop-outs' if they:

1. Become lost to follow-up or discontinues intervention.

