## 4. Trial Schedule

During Pre-Screening, the parent/legal guardian will complete the structured interview, CDISC.

Once the diagnosis of ADHD (inattentive/combined subtype) has been made, the parent/legal guardian will complete the following questionnaires during the baseline stage (Week 1):

a. ADHD Rating Scale

b. Child Behavior Checklist

If the child has ever been placed in the school's Learning Support Program and/or is currently failing a subject, he/she will be screened using the Kaufman Brief Intelligence Test.

The assessment schedule is summarized in Table 1 section 6.6.

Once the diagnosis of ADHD has been made, the following assessments will be completed by different informants:

CLINICIAN:

1. ADHD Rating Scale (ADHD- RS)
2. Clinical Global Assessment Scale (CGAS)
3. Clinical Global Impression - Severity Scale (CGI-S)
4. Clinical Global Impression – Improvement Scale (CGI-I)
5. Pediatric Adverse Event Rating Scale (PAERS) from week 8 onwards as there will be nothing to report at the first session.

PARENT:

1. ADHD Rating Scale (ADHD-RS)
2. Child Behavior Checklist (CBCL)

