| Clinical Global Impression - Improvement Scale                            | Group 1     |                     | XX       | XX           |              | X       |             | X         |         |
|                                                                           | Group 2     |                     |          |              | X            |         | X           |           | X       |
| ADHD Rating Scale                                                         | Group 1     |                     | XX       | XX           |              | X       |             | X         |         |
|                                                                           | Group 2     |                     |          |              | X            |         | X           |           | X       |
| Pediatric Adverse Event Rating Scale (PAERS)                              | Group 1     |                     |          | X            |              | X       |             | X         |         |
|                                                                           | Group 2     |                     |          |              | X            |         | X           |           | X       |

NB: All assessment visits will be completed accordingly to the assessment week within the window period of +/- 5 working days.

Figure 1: Study Visit and Procedure for Both Groups

**Appendix A****Schedule 1: Gantt schedule of Phase 2 overall study design and timelines for intervention & control groups.**[figure not shown]**Assessments for both intervention and control group**

| Week 0                      | Week 1
(+/- 5 work days)   | Week 8
(+/- 5 work days)                              | Week 16
(+/- 5 work days)  | Week 20 (Intervention)
Week 28 (Control)
(+/- 5 work days) | Week 24 (Intervention)
Week 32 (Control)
(+/- 5 work days) |
|------------------------------------|---------------------------------------------|------------------------------------------------------------------------|---------------------------------------------|-----------------------------------------------------------------------------------------------------|-----------------------------------------------------------------------------------------------------|

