## **8. Treatment of Subjects**

### **8.1 Specific Restrictions**

1. There are no dietary restrictions.
2. There is no limitation in the physical activity of the subject.
3. Intake of methylphenidate, atomoxetine and tricyclic anti-depressant are to be avoided 1 month before and during the study since these medications can improve ADHD symptoms. The parent/legal guardian and/or the subject will be asked about this during each study visit. If there is a need for these medications to be prescribed to the subject then the subject will be withdrawn from the study.
4. Intake of polyunsaturated fatty acids (PUFA) supplement intake (e.g. Omega-3 oil, flax seed oil, cod liver oil) which can improve ADHD symptoms are also to be avoided 3 months before and during the study. These supplements are receiving attention as a complementary approach to managing ADHD. While not a primary empirical based treatment and efficacy outcome varied, the study team will exclude subjects who are taking these supplements in the past 3 months, if they have been taking them regularly for a period longer than 2 weeks, to ensure that any improvement in inattentive symptoms is not due to the supplementation.
5. Intake of traditional Chinese medication (TCM) treatment is also to be avoided 1 month before and during study. Similar to PUFA, these alternative treatments could also manage inattentive symptoms. Therefore, subjects will be withdrawn from the study if these supplements are taken in the past 1 month.
6. From the literature, the potential risks to the BCI may include seizure or destabilization of the individual's mood state. To minimize such risk, subjects with history of seizure or severe psychiatric disorder will be excluded in this study.

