## **9. Safety Measurements**

### **9.1 Definitions**

#### **9.1.1 Adverse Events**

The Pediatric Adverse Event Rating Scale will be used to assess adverse events.

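### The only active adverse-event enquiry is the PAERS, first about 7 weeks into training and next 12 weeks later, while the 27 BCI attendances per child carry no adverse-event question

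*Protocol*

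**What the plan says.** **Collection.** Section 9.2.1 sets a continuous window: "AEs will be collected from the time the informed consent and assent forms have been signed until the end of the study". It then describes the sources: "This will include AEs spontaneously reported by the subject and / or observed by the parents and clinicians".

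**Instrument.** Section 9.1.1 names one tool: "The Pediatric Adverse Event Rating Scale will be used to assess adverse events". Section 4 lists it among the clinician's assessments and starts it "from week 8 onwards as there will be nothing to report at the first session". Table 1 places it at weeks 8, 20 and 24 for the intervention group and at weeks 16, 28 and 32 for the control group, with a window of 5 working days either side.

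**Exposure.** Sections 5.1 and 5.2 plan 24 sessions over 8 weeks (at least 20 to be completed), then three monthly boosters. Control children start at week 9. Section 12.1 has all interventions carried out in rooms within the clinic.

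**Questioning at attendances.** Section 3.3, on treatments that can improve ADHD symptoms, says: "The parent/child will be asked about this each time they turn up at the clinic". Section 8.1 repeats the enquiry for medication. Neither extends it to adverse events.

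**Use of the data.** Section 2.2.1 makes safety of the BCI a secondary objective, and section 2.3.1 makes AEs and SAEs the safety endpoint. Section 11.2.3 plans frequencies and percentages of events in a side-effect checklist, pooled over all children with at least one BCI session. The checklist is not defined; the PAERS is the most plausible reading.

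**The concern.** A safety objective for a training device is best served by asking about events close to the exposure. Here the exposure takes place at frequent supervised attendances, about three a week during training, but the structured question is put only at the assessment visits. The therapist mentioned in section 1.1 has no adverse-event role anywhere in section 9.

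The events at risk are mild and short-lived ones during or soon after a session. A child of 6 to 12 may not volunteer them, a parent may not think them worth mentioning, and weeks later they may be forgotten. Because the planned summary is limited to checklist events, one that was volunteered in between and then not repeated at the PAERS visit has no stated place in the reported table. The published rates could then look more reassuring than the children's experience was.

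**Working it through.** The protocol states no figure for this point, so none can be reproduced. The check is a count of contacts and a subtraction of schedule weeks.

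**Inputs**
- Training starts at week 1 (intervention, taken from the schedule) and week 9 (control, section 5.2).
- PAERS weeks are 8, 20, 24 and 16, 28, 32 (Table 1).
- The visit window of 5 working days either side is about 1 calendar week (Table 1 note).
- Sessions: 24 in training plus 3 boosters (sections 5.1 and 5.2).
- Enrolment: 172 children (section 3).

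**Intervals between active enquiries**

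| Interval | Intervention | Control | Weeks | With windows |
|---|---|---|---|---|
| Start of training to first PAERS | 8 − 1 | 16 − 9 | 7 | 7 + 1 = 8 |
| First to second PAERS | 20 − 8 | 28 − 16 | 12 | 12 + 1 + 1 = 14 |
| Second to third PAERS | 24 − 20 | 32 − 28 | 4 | 4 + 1 + 1 = 6 |

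In the first row only the PAERS visit is allowed to be late. In the others the earlier visit is taken at the start of its window and the later one at the end. The longest interval is the second, which covers the boosters.

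**Contacts per child**
- Planned BCI attendances: 24 + 3 = 27. At the minimum of 20 training sessions: 20 + 3 = 23.
- PAERS enquiries: 3.
- Over all children: 27 × 172 = 4,644 planned attendances against 3 × 172 = 516 PAERS. These count opportunities to ask; they do not count missed events.

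**Which route catches which event**
- Deaths and unanticipated problems have 24-hour and 7-day reporting (section 9.2.2) and do not wait for the PAERS. The clock runs from the investigator's first knowledge, and no text requires session staff to pass on what they see.
- Events meeting the SAE criteria in section 9.1.3 belong to the safety endpoint whenever they occur.
- A mild event volunteered by the child or noticed by a parent can be collected at any time under section 9.2.1, but section 11.2.3 does not say it will be tabulated.
- A mild event that nobody volunteers reaches the data only if it is recalled at the next PAERS.

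**Size of the loss.** The recall period of the PAERS is not stated, nor is any expected rate of complaints or any proportion still remembered at the visit. A percentage would be the product of assumed values, so none is given.

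**The case against.** The strongest reply is that nothing in section 9 is contradictory and that collection is not confined to the PAERS. It is continuous by text. The list of sources in section 9.2.1 is introduced as inclusive, so an event seen by session staff is not shut out. Section 12.1 has a parent, who is a named source, come with the child to every visit. Section 6.5 leaves investigators and study personnel unblinded, so a parent can speak to them without harming the blind. Section 9.3 makes the investigator responsible for safety monitoring, and section 9.4 gives parents a contact route. All of this stands.

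It rules out two stronger readings that a reader might infer. One is that the investigator has no planned information between week 1 and week 8. In fact there is a route by spontaneous report; what is missing is a planned active enquiry. The other is that the safety objective as a whole is answered from late recall. The endpoint is AEs and SAEs, and serious or unanticipated events do not depend on the PAERS. Only the reported checklist rates rest largely on recall.

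The risks that the protocol names are also weak examples. Section 8.1 says "From the literature, the potential risks to the BCI may include seizure or destabilization" of mood, but it excludes children with a history of seizure or severe psychiatric disorder, and a seizure with a parent in attendance is unlikely to need prompting. The argument concerns milder complaints.

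Two smaller points stand as well. The week 8 and week 20 assessments fall at the ends of the intervention group's training and booster blocks (weeks 16 and 28 for controls), so a PAERS may coincide with a session and 27 unquestioned attendances may be a slight overcount. And section 9.2.1 does not limit its clinicians to the blinded raters.

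What the reply does not supply is an adverse-event question at any session, a duty on session staff to record events, or a place in the planned summary for events outside the checklist. The blinding instruction in section 6.5 may even make families guarded about session-related complaints when the blinded clinician rates the PAERS, though the protocol gives no evidence on this.

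**Conclusion.** The point holds as a low-cost improvement to adverse-event ascertainment and reporting; it does not show an error in the protocol. Active enquiry is made 3 times per child against 27 planned BCI attendances, first about 7 weeks into training (8 with the window) and next after 12 weeks (up to about 14). Since section 11.2.3 covers only checklist events, mild or transient events can be under-counted, by an amount that the document does not allow one to compute.

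This assumes that the side-effect checklist is the PAERS, that training begins at week 1 or week 9 as scheduled, and that no session form, unseen here, already carries an adverse-event question. The primary efficacy analysis is not affected.

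**What to change.** - **Section 9.2.1:** name the BCI session staff as a source. At every training and booster session, alongside the existing question on prohibited treatments, have them ask one open question about adverse events during the session and since the last visit. Record each event in the CRF with its date and session number, and pass it to an unblinded investigator rather than to the blinded raters.
- **Section 11.2.3:** state that the pooled safety summary covers all collected AEs and SAEs as well as the checklist items, and list the session-recorded events separately. Define the checklist, by name if it is the PAERS.

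The cost is one question at attendances that already take place and already include a questioning step, one CRF entry and one listing. No extra visits or staff are needed.

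The drawback is unequal ascertainment: more minor events will be recorded during BCI than during the wait. Session-recorded events must therefore not be used to compare arms. The planned summary is pooled, so it makes no such comparison; any that is added later should use only instruments applied equally in both arms.

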### **9.2.2 UPIRTSO**

#### **1. Urgent Reporting:**

All problems involving local deaths, whether related or not, should be reported immediately – within 24 hours after first knowledge by the Investigator.

#### **2. Expedited Reporting:**

All other problems must be reported as soon as possible but not later than 7 calendar days after first knowledge by the Investigator.

## **9.3 Safety Monitoring Plan**

The investigator is responsible for monitoring the safety of study participants who have entered this study and to take appropriate action concerning any event that seems unusual. Subjects will be followed up if:

- Subject has at least one SAE or subject withdrawn from the study as a result of an AE, until the event has been resolved, subsided, stabilized, disappeared, the event is otherwise explained, or the subject is lost to follow up
- Or, in the case of other non-serious AEs, until they complete the study or they are lost to follow up

## **9.4 Complaint Handling**

Parents/legal guardians of the subject will be provided with the contact numbers of the PI and the DSRB secretariat. Complaints about the conduct of the study will be reported directly to the PI for immediate and proper actions.

## **9.5 Criteria for Stopping the Research**

Subjects are not expected to experience any problems when participating in these training games. There is no invasive procedure involved. The research however may be suspended if any part of the protocol is breached or if there is any violation of standard research ethics.

Parents can undergo a review with the study psychiatrist to consider dropping out of the study if:

1. ADHD-RS raw score increases by 25% as assessed by the clinician and/or
2. CGI scores are between 5 and 7 inclusive.

## **10. Data Analysis**

### **10.1 Data Quality Assurance**

To ensure data quality entered data will be systematically checked by the data management staff and validated against rules which are built into the database system. Any discrepancies will be channeled to relevant parties for resolutions. All discrepancies will be resolved prior to database lock and data analysis. Quality control audits of all key safety and efficacy data in the database will be made before database lock.

## **11. Sample Size and Statistical Method**

### **11.1 Determination of Sample size**

Based on a moderate effect size of 0.5 on ADHD Rating Scale inattentive score improvement rated by clinicians, power of 80% and type I error of 5%, a sample size of approximately 80 subjects per group is necessary. This includes an allowance for up to 20% losses to follow-up.

### **11.2 Statistical Analysis Plans**

#### **11.2.1 General considerations**

All statistical analyses will be carried out on an intention-to-treat (ITT) basis unless otherwise stated. An ITT set is defined as all randomized subjects. The treatment group of subjects in the ITT set is the planned treatment group, i.e., according to the randomization list planned prior to the study commencement. All tests of hypotheses will be two-tailed. Statistical significance testing will be performed at the 0.05 level. All statistical analyses will be performed using SAS Version 9.3 or higher. Statistical analysis and programming support will be provided by the Singapore Clinical Research Institute (SCRI).

#### **11.2.2 Demographic and baseline characteristics**

Demographic data and baseline characteristics will be summarized by descriptive statistics and presented by randomisation group. Continuous variables will be summarized using mean and standard deviation. Categorical variables will be summarized using the number of observations and percentages. Eligibility criteria deviation and subject's accountability will be tabulated and reported in CONSORT (Consolidated Standards of Reporting Trials) flow chart.

#### **11.2.3 Analysis of primary and secondary endpoints**

Change in the inattentive score on the ADHD Rating Scale as rated by clinicians at week 8 will be compared between the intervention group (post-BCI) and control groups (pre-BCI) using the two sample t test. Mean difference of the changes between the two groups and its associated 95% confidence interval will be reported. Comparison of change scores for the continuous secondary outcomes at week 8 between the two groups will also be conducted by using the two sample t test or Mann-Whitney U test, where appropriate. Chi squared test or Fisher's exact test, where appropriate, will be used for categorical secondary outcomes.

Booster effect will be analyzed by first pooling paired data before and after the boosters in the two groups. Change in efficacy endpoints as rated by clinicians and parents at week 20 from week 1 in the intervention arm and changes at week 28 from week 9 in the waitlist control group. These pooled changes before and after the boosters will be summarized; and comparisons of efficacy endpoints pre and post boosters will be made in the pooled data by using the paired t test or Wilcoxon signed rank test, where appropriate. The above will also be conducted at week 24 from week 1 in the intervention arm and week 32 from week 9 in the waitlist control to assess the effect the sustainability of the effect of the BCI system.

The longitudinal ADHD ratings, and other clinician's scales will be explored by the generalized estimating equations approach, both assessing the time trend and the difference in time trend between groups.

Frequency and percentage of the adverse events highlighted in the side effect checklist will be summarized for the pooled sample since the BCI program is administered to all subjects for all those that receive at least one BCI session.

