### **2.1.2 Primary Endpoint**

The primary outcome of this study will be the change in the inattentive score on the ADHD Rating Scale as rated by the clinicians from week 1 to week 8.

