#### **6.4 Randomisation**

This is a randomised, single-blind study. When the informed consent and assent forms are signed and the eligibility criteria are confirmed, the subject will be randomized to intervention or control group at a 1:1 allocation ratio, giving approximately 86 subjects in each group. Balanced treatment assignments will be achieved using permuted block randomisation, stratified by gender and age, across one study site. The stratification factor for age will be categorized into two groups, aged 6-9 years old and aged 10-12 years old. Block size will be determined by the study statistician and will not be made known to the clinical investigators or site personnel. The randomization procedure, done after obtaining consent, assent and CDISC results at Week 0, will assign a unique “subject number” to each child.

Implementation of randomisation will be carried out via a web-based program at SCRI. Authorized study centre personnel will randomise the patient via a password-protected internet web site. The randomisation system will then determine the treatment arm and provide the subject number to be used for the patient. The site monitor/CRA will be informed immediately in the event that the web randomization is not successful. Back-up randomisation envelopes will be provided to the site in case of internet failure.

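### The primary change-score t test is valid, but it fixes the baseline slope at 1 and leaves out the stratification factors; ANCOVA on the same data is generally more precise

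*Protocol*

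**What the plan says.** Protocol section 2.1.2 defines the primary outcome as "the change in the inattentive score on the ADHD Rating Scale as rated by the clinicians from week 1 to week 8". Section 11.2.3 says that this change "will be compared between the intervention group (post-BCI) and control groups (pre-BCI) using the two sample t test", and adds: "Mean difference of the changes between the two groups and its associated 95% confidence interval will be reported". No covariate is named for this analysis or anywhere else in section 11.2. The only model-based analysis is an exploratory GEE of time trends, with no stated adjustment for baseline or strata.

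Section 6.4 says: "Balanced treatment assignments will be achieved using permuted block randomisation, stratified by gender and age, across one study site". The two age groups are 6-9 and 10-12 years. Section 6.4 also has children "randomized to intervention or control group at a 1:1 allocation ratio, giving approximately 86 subjects in each group".

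The sample size in section 11.1 is "Based on a moderate effect size of 0.5 on ADHD Rating Scale inattentive score improvement rated by clinicians", with "power of 80% and type I error of 5%, a sample size of approximately 80 subjects per group is necessary". That number already contains a 20% allowance for loss to follow-up. Section 11.2.1 makes all tests two-sided at 0.05.

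**The concern.** A change score uses the baseline, but with a coefficient fixed at 1. When the week 1 and week 8 scores are imperfectly correlated, the best-fitting slope usually differs from 1, and three things follow.

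- **Precision.** The residual variance is larger than it need be, so the primary confidence interval is wider than it need be.
- **Chance imbalance.** Randomisation balances gender and age group, not severity. If one arm starts worse by chance, regression to the mean makes it appear to improve more, and the t test credits that to treatment or charges it against treatment.
- **Strata.** Factors considered important enough to stratify on are left out of the analysis. If they predict change, the unadjusted standard error is too large.

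At stake is power and the stability of the primary estimate, not the validity of the test.

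**Working it through.** **Inputs from the protocol.** Standardised effect 0.5 on score improvement, 80% power, two-sided 5%, 20% loss (sections 11.1 and 11.2.1); 86 per arm enrolled (section 6.4).

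**Not given, so assumed.** The correlation r between week 1 and week 8 clinician scores, taken as 0.4 to 0.9; and the ratio k of the week 8 SD to the week 1 SD, taken first as 1.

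**1. The plan's own figure.** Normal approximation: n = 2(1.96 + 0.8416)²/0.5² = 62.8, so 63 per arm; 63/0.8 = 78.75, so 79. The t-based solution is 63.8, so 64 per arm; 64/0.8 = 80. The stated 80 reproduces. With 86 enrolled, 86 × 0.8 = 68.8, so about 68 evaluable. The planned t test then has 82.5% power (80.1% at 64 per arm).

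**2. Variance ratio with equal SDs (s).** Change score: 2(1 − r)s². ANCOVA residual: (1 − r²)s². Ratio ANCOVA/change = (1 − r²)/[2(1 − r)] = (1 + r)/2. For the same true difference, the standardised effect becomes 0.5/√[(1 + r)/2].

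| r | Variance ratio | SE ratio | ANCOVA power, 64 per arm | ANCOVA power, 68 per arm |
|---|---|---|---|---|
| 0.4 | 0.70 | 0.837 | 91.8% | 93.3% |
| 0.5 | 0.75 | 0.866 | 90.0% | 91.7% |
| 0.6 | 0.80 | 0.894 | 88.1% | 89.9% |
| 0.7 | 0.85 | 0.922 | 86.1% | 88.1% |
| 0.8 | 0.90 | 0.949 | 84.1% | 86.2% |
| 0.9 | 0.95 | 0.975 | 82.1% | 84.4% |
| t test, any r | 1 | 1 | 80.1% | 82.5% |

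**3. Unequal SDs.** The ratio is k²(1 − r²)/(1 + k² − 2rk). The denominator minus the numerator equals (1 − rk)², which is never negative, so the large-sample ratio cannot exceed 1. It equals 1 only when the true slope rk is 1.

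- k = 0.8: 0.57 at r = 0.5, 0.63 at r = 0.7, 0.61 at r = 0.9.
- k = 1.25: 0.84 at r = 0.4, 0.89 at r = 0.5, 0.98 at r = 0.7, 1.00 at r = 0.8, 0.95 at r = 0.9.

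**4. Chance imbalance.** With equal SDs, the change-score estimate moves by −(1 − r) per unit of baseline difference between arms. One standard error of that difference at 64 per arm is s√(2/64) = 0.177s. The planned effect is 0.5√[2(1 − r)]s. At r = 0.5 the shift is 0.5 × 0.177 = 0.088 against 0.5, or 18% of the planned effect. At r = 0.7 it is 0.3 × 0.177 = 0.053 against 0.387, or 14%.

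**5. Simulation** (64 per arm, equal SDs, 6,000 runs per setting). Power, t test against ANCOVA: 80.1% and 93.8% (r = 0.3), 80.2% and 89.2% (r = 0.5), 79.3% and 85.1% (r = 0.7). Type I error was about 5% for both. The slope of the change-score estimate on the baseline difference was −0.71, −0.50 and −0.30; for ANCOVA it was about 0.

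**The case against.** The plan is internally consistent: the endpoint is a change, the sample size is set on improvement, and the test compares changes. The stated size reproduces, and 86 per arm already exceeds the power target. All of that stands.

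A reader might go further in several ways that the protocol does not support.

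- **That the test ignores baseline, or is biased.** A change score subtracts baseline. The bias is conditional on the realised imbalance; over randomisations the estimate is unbiased, and the t test's standard error already contains that variability.
- **That stratifying and then not adjusting makes the standard error wrong by a known amount.** Stable effects of age or gender on the level of the score cancel in a change score. The standard error is too large only if these factors predict change, which is conservative and cannot be sized from the protocol.
- **That a gain of some ten points is assured.** The upper figures need r near 0.4 and equal SDs, neither of which the protocol gives. Entry on a diagnosis could restrict the baseline range and make k exceed 1, where the gain can be almost nil. The only reliability figure, above 0.9 in section 1.1, is for parent and teacher scales in the pilot; if the clinician score behaved similarly, the gain would be about 2 points.
- **That every continuous secondary outcome gets the same t test.** Section 11.2.3 allows a Mann-Whitney U test where appropriate.

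None of this defeats the change to the primary analysis. The protocol itself names the test, so the choice has not been left to a later SAP.

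**Conclusion.** The concern holds as a matter of efficiency and of sensitivity to chance imbalance, not of validity. Over the assumed range of r and with equal SDs, ANCOVA cuts the standard error by about 16% (r = 0.4) to 2.5% (r = 0.9). At about 68 evaluable per arm that is worth between 11 and 2 percentage points of power. These figures adjust for baseline only. The size depends on r and on the SD ratio, both unknown; the direction does not, because in large samples ANCOVA is never less precise than the change score. The planned sample size does not fail and need not change. The improvement costs almost nothing, so it should be made.

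**What to change.** Before database lock, amend section 11.2.3 so that the primary analysis is an ANCOVA of the week 8 clinician inattentive score with terms for arm, week 1 score, gender and age stratum (6-9, 10-12), reporting the adjusted mean difference and its 95% confidence interval. Modelling the change with the same covariates gives the same treatment estimate, so the endpoint in section 2.1.2 can stay as worded. Keep the t test on change as a sensitivity analysis.

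Use the same model for the continuous week 8 secondary outcomes (parent ADHD-RS inattention, CBCL inattention, C-GAS). Retain the non-parametric provision where it is needed and for the ordinal CGI scores.

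The cost is wording plus three degrees of freedom out of 126 at 64 per arm. The week 1 score is already needed to compute the change, and gender and age are already needed to randomise, so no child is lost, no visit is added and no larger sample is required. The timing matters: adjustment chosen after the results are seen would not be credible.
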